## Abstract

**Background:**

Preventing early invasive mechanical ventilation (IMV) in preterm infants is critical for reducing bronchopulmonary dysplasia (BPD) and improving outcomes. While delayed cord clamping (DCC) enhances cardiopulmonary stability and minimally invasive surfactant administration (MISA) reduces IMV dependence, evidence on their combined efficacy in extremely preterm infants (<30 weeks gestation) with neonatal respiratory distress syndrome (NRDS) remains limited. We hypothesize that integrating DCC with MISA will synergistically reduce BPD incidence compared to immediate cord clamping (ICC) with either MISA or tracheal intubation-based surfactant delivery.

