### Research grouping

Patients were divided into three groups based on the study's time phases and the differences in treatment they received after birth:

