### Sample size calculation

Our hospital has previously conducted a prospective multicenter clinical study comparing MISA and tracheal intubation in the early stages. The results indicated that the incidence of BPD in premature infants with a gestational age of less than 30 weeks was 29% in the MISA group (*n* = 31) and 70% in the tracheal intubation group (*n* = 20). Assuming the BPD incidence rate (p_1_) in the ICC + MISA group for this study is 29%, and the incidence in the DCC + MISA group (p_2_) decreases by 15%–14%, we will set the Type I error (α) at 0.05 and the Type II error (β) at 0.2. With a sample size ratio (k) of 3:1 between the DCC + MISA and ICC + MISA groups, the sample size calculation formula is:$$n_{2}=\frac{{\left(z_{1-a/2}+z_{1-\beta }\right)}^{2}[\;p_{1}(1-p_{1})/k+p_{2}(1-p_{2})]}{{\left(\;p_{1}-p_{2}\right)}^{2}}$$*n*_1_ = *k* × *n*_2_.

Where z_(1−*α*/2)_ = 1.96 and _z(1−*β*)_ = 0.84.

This results in a sample size of 66 for the DCC + MISA group and 198 for the ICC + MISA group. Assuming a 10% loss to follow-up, the adjusted sample sizes will be 74 for the DCC + MISA group and 222 for the ICC + MISA group. Additionally, the sample size for the ICC + tracheal intubation group is also set at 222 cases.

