DCC not only enhances the transfer of blood from the placenta to the fetus, improving hemoglobin reserves in premature infants, but it also stabilizes the establishment of pulmonary circulation in the early postnatal period. Since placental circulation provides 30%–50% of cardiac blood flow, immediate clamping of the umbilical cord can lead to a significant drop in venous return and cardiac output. DCC facilitates a smoother transition until premature infants can establish effective pulmonary ventilation and circulation. Thus, DCC serves as a crucial component of early respiratory and circulatory management for these infants. This study aims to determine whether the simultaneous application of DCC and MISA further enhances survival and prognosis in premature infants. Given our recent implementation of DCC for infants born before 30 weeks, we designed a NICU quality improvement study to evaluate the efficacy of DCC combined with MISA by comparing prospective and retrospective cohorts.

Despite the potential of this study, there are some limitations to consider. As a quality improvement study, data for the ICC and MISA and ICC and tracheal intubation groups were collected retrospectively, which may introduce biases due to variations in hospitalization years and treatment approaches. Furthermore, the retrospectively collected data are based on the diagnosis, treatment, and evaluation conducted by clinicians, and there may be variations in this process. To minimize these discrepancies, we limited the study to preterm infants from the past six years for the retrospective cohort. Additionally, both the prospective and retrospective cohorts adhered to the same inclusion and exclusion criteria to reduce intergroup differences and enhance the validity of the conclusions.

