## Conclusion

If the combination of DCC and MISA proves effective in reducing BPD in premature infants born before 30 weeks and enhances their prognosis compared to the ICC and MISA or ICC and tracheal intubation groups, this finding will provide a theoretical foundation for improving the quality of care in the NICU and optimizing early respiratory and circulatory management for small gestational age premature infants.

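### The synergy hypothesis cannot be tested with these three groups, and the text does not name DCC+MISA versus ICC+MISA as the deciding contrast

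*Protocol article*

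**What the plan says.** The hypothesis, in the Background paragraph of the abstract, is that "integrating DCC with MISA will synergistically reduce BPD incidence compared to immediate cord clamping (ICC) with either MISA or tracheal intubation-based surfactant delivery".

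Under Research grouping, "Patients were divided into three groups based on the study's time phases and the differences in treatment they received after birth". The three groups are ICC + tracheal intubation (2017–2020), ICC + MISA (2021–2024) and DCC + MISA (August 2025 to October 2027). No group has DCC with surfactant given through a tracheal tube.

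The closing Conclusion says what follows if the combination proves effective "compared to the ICC and MISA or ICC and tracheal intubation groups". The Discussion words the aim more modestly, as "whether the simultaneous application of DCC and MISA further enhances survival and prognosis in premature infants".

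The Sample size calculation reports BPD rates from an earlier study by the same hospital: "29% in the MISA group (*n* = 31) and 70% in the tracheal intubation group (*n* = 20". It takes 29% for ICC+MISA and 14% for DCC+MISA and sizes that contrast only. The intubation group is set at 222 without a calculation of its own.

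The Statistical analysis section describes three-group comparisons and an adjusted odds ratio for DCC+MISA on BPD. It does not say which group is the reference or which pairwise contrast decides.

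**The concern.** Two things follow from the three-group layout.

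First, synergy means that the two components together do more than their separate effects would predict. Cord management and surfactant route form a two-by-two table, and the study observes three of its four cells. The effect of DCC without MISA is never seen, so no result could confirm or refute the hypothesis as worded.

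Second, the two comparators answer different questions. DCC+MISA versus ICC+MISA isolates the step from immediate to delayed clamping, apart from whatever else changed between the two periods. DCC+MISA versus ICC+intubation changes clamping and surfactant route together, so it can be clearly positive when clamping contributes nothing. Where the text joins the two with *or* and names no deciding contrast, a reader can take a positive intubation contrast as support for the combination. At stake is whether a favourable conclusion would say anything about adding DCC in a unit that already uses MISA.

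**Working it through.** **Step 1. The plan's own figure.** Inputs from the Sample size calculation: p1 = 0.29, p2 = 0.14, k = 3, z = 1.96 and 0.84.

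n2 = (1.96 + 0.84)² × [0.29 × 0.71/3 + 0.14 × 0.86] / 0.15² = 7.84 × [0.0686 + 0.1204] / 0.0225 = 65.87, rounded up to 66.

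n1 = 3 × 66 = 198. With 10% loss, 66/0.9 = 73.3, rounded up to 74, and 3 × 74 = 222. The stated 66/198 and 74/222 reproduce. The sample size is not at issue here, and it is built on DCC+MISA versus ICC+MISA.

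**Step 2. What the missing cell would have to be.** With 70%, 29% and 14% in the three observed cells, the DCC+intubation rate that would mean no interaction depends on the scale:

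- Risk difference: 70% − 15 points = 55%.
- Odds ratio: (0.14/0.86)/(0.29/0.71) = 0.399. Applied to the odds 0.70/0.30 = 2.333 this gives 0.930, a rate of 0.930/1.930 = 48%.
- Risk ratio: 0.70 × 0.14/0.29 = 34%.

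The study observes nothing to set against any of these.

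**Step 3. What each contrast shows if DCC does nothing.** DCC+MISA is set to 29%, the same as ICC+MISA. The probability of a significant result in the favourable direction (two-sided 5% Pearson chi-square) was found by exact enumeration of the two binomials. The sizes are 66 versus 198, the evaluable numbers before inflation. Rates below 70% are assumptions, shown because the 70% rests on 20 infants.

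| Comparator and its BPD rate | No continuity correction | With continuity correction |
|---|---|---|
| ICC+intubation, 70% (article) | above 99.9% | above 99.9% |
| ICC+intubation, 50% (assumed) | 86% | 82% |
| ICC+intubation, 45% (assumed) | 64% | 58% |
| ICC+intubation, 40% (assumed) | 36% | 30% |
| ICC+intubation, 35% (assumed) | 14% | 10% |
| ICC+MISA, 29% | 2.3% | 1.6% |

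With the full 74 versus 222 the figures are slightly higher: at 45%, 69% uncorrected and 64% corrected. A simulation of all three groups together at 66/198/198 (400,000 runs, uncorrected) gave the chance of at least one favourable result as above 99.9% at 70%, 86% at 50%, 36% at 40% and 14% at 35%. These are almost the same as the intubation contrast alone, so that contrast would drive any either-comparator reading.

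**The case against.** The strongest reply is that no passage says one significant contrast is enough. In the abstract, *either* may simply name the two surfactant routes that accompany ICC. In the Conclusion, *or* may list two comparator groups that the combination is expected to beat. This stands. A reader might infer a rule under which a win over either comparator counts, but the article states none. The probabilities above describe what such a reading would do, not a procedure the article has adopted.

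A reader might also infer that DCC would be credited with a gain due to MISA. The text does not support that either: it attributes any benefit to the combination, and comparing whole regimens is legitimate in a quality improvement study. Nor does any analysis or concluding sentence claim synergy. The word appears once, in the abstract's hypothesis.

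The contrast that matters is already the one the study is sized on, and the Discussion's aim of further benefit fits it. An unnamed reference group could be a detail left to a fuller document.

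What remains is narrower. No analysis plan can supply a missing group, so the hypothesis as worded stays untestable. The Conclusion is a conditional statement of what would justify the claim, and it leaves open which comparison carries it.

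**Conclusion.** The point holds as a mismatch between the stated hypothesis and conclusion and what the design can show. It is not an error in the sample size or evidence of a faulty decision rule. Interaction between DCC and MISA cannot be estimated from these groups. The design can estimate the effect of DCC given MISA, but because the two MISA groups come from successive periods, that effect is confounded with calendar time.

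If the intubation contrast were taken as support, a DCC with no effect would still yield a favourable result with probability above 99.9% at the article's 70% versus 29%, and about 86% to 14% as the assumed intubation rate falls from 50% to 35% (66 versus 198, uncorrected). The figure for ICC+MISA is about 2%. The calculation assumes 29% in both MISA groups, no drift over time, and no covariate adjustment. The continuity correction lowers the intermediate figures by about 3 to 6 points and does not change the conclusion.

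**What to change.** 1. In the abstract's hypothesis, replace *synergistically* with wording such as *further, beyond ICC+MISA*.
2. Name DCC+MISA versus ICC+MISA, the contrast already used for sizing, as the deciding comparison for BPD, and make ICC+MISA the reference group for the adjusted odds ratio.
3. Reword the Conclusion so that the claim of effectiveness depends on that comparison.
4. Report DCC+MISA versus ICC+intubation as a supportive estimate of the whole change in care between the periods.

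This needs no fourth group, no additional infants and no new data. The cost is a narrower claim: the study could speak to the added benefit of DCC where MISA is used, subject to the period difference, but not to synergy.

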**Methods and design:**

This is a single-center quality improvement study evaluating three treatment regimens for neonates with NRDS born at a gestational age of <30 weeks: (1) Retrospective data collection of cases treated with the conventional approach of ICC + tracheal intubation between 2017 and 2020 (*n* = 222); (2) Retrospective data collection of cases treated with ICC + MISA between 2021 and 2025 (*n* = 222); (3) Planned collection of medical records of cases treated with DCC + MISA between 2025 and 2027 (*n* = 74).The study aims to assess the incidence of BPD and survival outcomes associated with each regimen. Meanwhile, it will compare the short-term efficacy, safety, and long-term outcomes of these three treatment strategies, thereby providing valuable evidence for clinical treatment decision-making.

**Discussion:**

Current research indicates that both DCC and MISA positively impact the prognosis of very premature infants and help reduce the incidence of BPD. However, there is limited research on whether the combined use of DCC and MISA can further improve survival rates and reduce the incidence of BPD in this vulnerable population. Our NICU has gradually implemented MISA in respiratory management since 2021 and adopted cord management with DCC since 2025. This study retrospectively analyzes data from previous groups: those receiving ICC with MISA, and those receiving ICC with tracheal intubation. We will compare this with prospective data from the DCC combined with MISA group to assess differences in BPD occurrence, other complications and overall outcomes. This study will also collect and analyze the annual application rates and operational success rates of MISA and DCC, so as to promote quality improvement in the NICU. Through this study, we aim to determine whether the combination of DCC and MISA offers greater benefits in improving the prognosis of very premature infants, ultimately providing a stronger foundation for early respiratory and circulatory management strategies for infants born before 30 weeks.

**Trial Registration:**

https://register.clinicaltrials.gov, Identifier:NCT07092319.

## Background

With the rapid advancement of neonatal intensive care technology, the survival rate of premature infants born at less than 30 weeks gestation continues to rise. However, the immaturity of various organ systems leads to a high incidence of complications, and long-term outcomes can often be less than optimistic (1). Consequently, enhancing both short-term and long-term prognoses for these infants through quality improvement initiatives has become a prominent focus in recent clinical research.

BPD is a critical complication in very premature infants, significantly affecting their future survival, as well as their respiratory and neurological development. Preventing and reducing the incidence of BPD is crucial for improving the overall prognosis of these infants (2). Ensuring postpartum respiratory and circulatory stability while minimizing exposure to early invasive mechanical ventilation is essential for preventing and reducing the incidence of BPD.

The management of respiratory and circulatory conditions in preterm infants begins with DCC in the delivery room. Compared to ICC, DCC facilitates the transfer of blood from the placenta to the infant, enhancing the adaptability of vital organs such as the heart, brain, and lungs. This practice supports a smoother transition from intrauterine to extrauterine life, promotes the conversion of respiratory circulation, and can reduce preterm infant mortality by 30%. Additionally, DCC decreases the incidence of complications such as intraventricular hemorrhage, necrotizing enterocolitis, and late-onset sepsis. It also increases blood volume, minimizes the need for blood transfusions, enhances iron storage, and lowers the risk of long-term neurodevelopmental issues. Therefore, DCC emerges as a viable strategy to enhance the perinatal prognosis of preterm infants (3–7).

However, there are limited reports in China regarding the implementation of DCC in premature infants born at less than 30 weeks gestation. Our hospital began adopting DCC for preterm infants in 2025 and has developed and standardized the operational procedures for this practice. However, relevant clinical studies have yet to be conducted. NRDS is a condition resulting from a deficiency of pulmonary surfactant in the alveoli. It is the most common respiratory issue encountered by very premature infants, who often experience progressively worsening respiratory distress shortly after birth. Treatment for NRDS involves respiratory support and the administration of exogenous PS. Traditionally, this is done through tracheal intubation. However, recent clinical studies have demonstrated that MISA offers several advantages over tracheal intubation (8). MISA effectively reduces the need for invasive mechanical ventilation within the first 72 h and plays a significant role in lowering the incidence of BPD (9).

With advancements in DCC and MISA technology in NICU settings, these approaches have become the preferred options for very premature infants who are breathing spontaneously at birth. To further assess the safety and effectiveness of DCC combined with MISA in our hospital's NICU for premature infants born at less than 30 weeks gestation, we propose this quality improvement study. The study aims to compare the incidence and prognosis of BPD and other complications before and after the implementation of DCC and MISA in the NICU.

Our hospital comprehensively implement the MISA since 2021 and has gained extensive clinical experience in treating NRDS in premature infants using this method. We previously conducted a prospective multicenter study comparing MISA with tracheal intubation for surfactant administration shortly after birth. The results indicated that the incidence of BPD and hemodynamically significant patent ductus arteriosus (hsPDA) was lower in the MISA group, highlighting its suitability for premature infants born at less than 30 weeks gestation (10, 11). Our hospital has gradually implemented DCC for premature infants prior to this research and has established a comprehensive protocol for its application in the delivery room and during surgical procedures. As a result, our NICU is well-equipped to perform DCC combined with MISA for infants born at less than 30 weeks gestation. Based on previous research findings, this study specifically targets premature infants under 30 weeks, a group that exhibits a relatively high incidence of BPD. By monitoring the respiratory and overall health outcomes of these infants following the application of DCC combined with MISA, we aim to evaluate the effectiveness of this NICU quality improvement measure in enhancing the prognosis of very premature infants.

## Methods

### Study design

For preterm infants with a gestational age of <30 weeks diagnosed with NRDS, along with the continuous advancement of diagnosis and treatment in the NICU, they were divided into 3 phases based on time and treatment methods:
From 2017 to 2020, retrospective data were collected from infants treated with ICC combined with tracheal intubation for pulmonary surfactant administration;In 2021, after the promotion of MISA in the NICU, retrospective data were collected from 2021 to 2025 of infants treated with ICC combined with MISA;Starting from 2025, as the NICU has popularized the operational procedures for DCC in preterm infants, a prospective cohort study is planned to be conducted, and data will be collected from infants treated with DCC combined with MISA.This study evaluated the incidence of BPD, survival status, and other comorbidities associated with each treatment regimen, so as to provide references for the formulation of clinical decisions regarding treatment option selection. The operational process of this study is illustrated in Figure 1.

**Figure 1 F1:**
[figure not shown]
Flow chart nof the study. This study is a single-center ambispective cohort study involving hospitalized preterm infants in the NICU of Peking University Third Hospital from Jan. 1, 2017, to Oct. 31, 2027. The subjects from Jan. 1, 2017, to Dec. 31, 2024, were included in the retrospective cohort study, while a prospective cohort study was conducted from Aug. 31, 2025 to Oct. 31, 2027.

### Participants

All infants participating in the study were selected using the same inclusion and exclusion criteria.

#### Inclusion criteria

① Infants of 23–29 + 6 weeks gestational age.② Born in Peking University Third Hospital, having spontaneous breathing after birth;③ Diagnosed as NRDS; NRDS is defined as progressive dyspnea that occurs after birth, with or without imaging evidence, excluding other causes of dyspnea.

#### Exclusion criteria

① Premature infants who have received tracheal intubation prior to the use of PS due to resuscitation or other reasons shortly after birth;② Premature infants with identified or confirmed congenital abnormalities (such as fetal edema, chylothorax, or neuromuscular disease) or severe birth complications (including hemorrhagic shock, air leakage, or early-onset sepsis) that impact respiratory function;③ Newborns who discontinue treatment or have incomplete information;④ Newborns involved in other intervention research studies.

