### Outcome measures

#### Primary outcome measure

The primary outcome is the survival rate and incidence of BPD at a corrected gestational age of 36 weeks.

Diagnosis and classification of bronchopulmonary dysplasia will follow the International Workshop BPD classification standards proposed by the US NICHD in 2019 (12).

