#### Secondary outcome measures

The secondary outcomes are as follows:
Rate of hsPDARate of air leakage, pulmonary hemorrhage, and infectious pneumoniaRate of late-onset sepsis with positive blood cultureRate of retinopathy of prematurity (ROP)Rate of grade III-IV periventricular intraventricular hemorrhage (IVH) and periventricular leukomalacia (PVL)Rate of neonatal necrotizing enterocolitis (IIA or above)Duration of NCPAP/NIPPV, duration of IMV, and days on supplemental oxygenLength of hospitalization and associated costs for care and treatmentMortality rates during the first week after birth and throughout hospitalizationHemoglobin and hematocrit levels within 24 h after birth, and timing of blood transfusions during hospitalizationIncidence and duration of hyperbilirubinemia

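### Excluding infants whose treatment stops or whose records are incomplete can take deaths out of the survival endpoint, and unequally across the three periods

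*Protocol article*

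**What the plan says.** In the protocol article, the third item under Exclusion criteria is "Newborns who discontinue treatment or have incomplete information". It sets no time limit and does not define discontinuation. The Participants section applies it throughout: "All infants participating in the study were selected using the same inclusion and exclusion criteria". The cohorts run from 2017 to 2020 and from 2021 to 2024 (retrospective), and from August 2025 to October 2027 (prospective).

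Under Primary outcome measure: "The primary outcome is the survival rate and incidence of BPD at a corrected gestational age of 36 weeks". Secondary outcome measures include mortality in the first week and during the hospital stay.

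On air leakage, the second exclusion item covers "severe birth complications (including hemorrhagic shock, air leakage, or early-onset sepsis) that impact respiratory function", while the secondary outcomes list "air leakage, pulmonary hemorrhage, and infectious" pneumonia. Neither place gives a time that separates the two.

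**The concern.** An eligibility rule should rest on what is known before, or independently of, the outcome. Stopping treatment and having an incomplete record both arise after birth, and both can follow from a poor clinical course. An infant whose treatment is discontinued and who then dies is, under the rule as written, not counted as a death; the infant is absent from the analysis. The same holds for an infant whose BPD status was never recorded.

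Two things are at stake. Survival, part of the primary outcome, can be overstated within a group. More seriously for a before-and-after comparison, the groups can be affected unequally. The Discussion relies on common criteria to make the cohorts alike. That argument works for baseline criteria. For a criterion met after birth it works only if discontinuation practice and record completeness were stable over about ten years and across retrospective and prospective collection. The Discussion itself concedes variation by year of hospitalization and in clinicians' assessment.

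**Working it through.** **The plan's own figures.** The document gives no rate of discontinuation, of incomplete records or of death. The nearest figure is the sample size, which reproduces and is not in dispute. With p1 = 0.29, p2 = 0.14, k = 3 and z-values of 1.96 and 0.84 (Sample size calculation):

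n2 = 2.80² × [0.29 × 0.71 / 3 + 0.14 × 0.86] / 0.15² = 65.87, so 66; n1 = 3 × 66 = 198.

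With the 10% allowance, 66 / 0.9 gives 74, and 3 × 74 = 222.

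**Effect on measured mortality (assumed inputs).** Let m be true mortality and f the share of deaths that follow discontinuation and are excluded. Assume that no survivor is excluded. Then

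measured mortality = (m − m·f) / (1 − m·f).

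For m = 0.15 and f = 0.3: (0.15 − 0.045) / (1 − 0.045) = 0.105 / 0.955 = 11.0%.

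| True mortality (assumed) | f = 30% | f = 50% | f = 70% |
|---|---|---|---|
| 10% | 7.2% | 5.3% | 3.2% |
| 15% | 11.0% | 8.1% | 5.0% |
| 20% | 14.9% | 11.1% | 7.0% |

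**False difference between periods.** At 15% true mortality in both periods, f = 50% in one and 30% in the other gives 8.1% against 11.0%, a gap of 2.9 points with no true difference. In another scenario, true mortality is 10% in both groups, and deaths after discontinuation that are excluded make up 8% of one group and 2% of the other. Measured survival is then 0.90 / 0.92 = 97.8% against 0.90 / 0.98 = 91.8%, a gap of 6.0 points. If the excluded shares are equal, the gap is 0. The sign depends on which period loses more deaths.

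**If some excluded infants survive.** Suppose 5% of the cohort die without discontinuation and a share d discontinue. Measured survival is 1 − 0.05 / (1 − d).

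| d | Measured survival | Overstatement if all who discontinue die | Overstatement if half die |
|---|---|---|---|
| 2% | 94.9% | 1.9 points | 0.9 points |
| 5% | 94.7% | 4.7 points | 2.2 points |
| 10% | 94.4% | 9.4 points | 4.4 points |

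The overstatement shrinks as more of the excluded infants survive. It vanishes if they die no more often than those retained.

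**BPD, as a bound only.** Suppose the 8 infants added for losses in the DCC + MISA group (74 − 66) were the ones with unknown BPD status; the document does not say this. The planned 14% of 66 is about 9 cases. With all 8 unaffected the rate is 9 / 74 = 12%; with all 8 affected it is 17 / 74 = 23%. The span of about 11 points compares with a planned effect of 15.

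**The case against.** The strongest reply is that the documents support a narrower point than the wording might suggest. Most of that reply stands.

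- A reader might infer that deaths are excluded. No section says so. An infant who dies on full treatment with a complete record stays in, and mortality is a listed outcome. Only deaths after discontinuation or with incomplete records are at risk.
- A reader might infer that survival is overstated in every group. That needs excluded infants to die more often than retained ones. It is plausible, but the document gives no data on it.
- A reader might see the air-leakage exclusion as contradicting the air-leakage outcome. The exclusion is limited to severe birth complications affecting respiratory function, so later leaks can still be counted. Only the dividing time is missing, which is a small point that the full protocol may settle.
- A reader might add early-onset sepsis to the list of lost endpoints. It is not an endpoint; only culture-positive late-onset sepsis is.
- A reader might see a conflict with the sample-size wording, "Assuming a 10% loss to follow-up". The allowance can equally mean collecting extra infants so that enough evaluable ones remain. The two passages are compatible on that reading.

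It is also fair that a record lacking clamping time or surfactant route cannot be assigned to a group, so some exclusion for incompleteness is unavoidable. None of this answers the central point: the third exclusion is a stated rule, it acts on events after birth, and no later analysis can use infants whom eligibility has already removed.

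**Conclusion.** The point holds in this limited form. The third exclusion item selects on events after birth that can depend on the course of illness, in a study whose primary outcome includes survival. Deaths after discontinuation, or with incomplete records, can leave the denominators. Survival can be overstated, and a false difference between groups can arise if discontinuation or completeness changed over 2017-2027.

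The size cannot be derived from the document. The assumed scenarios show it could be a few points: measured mortality of 11%, 8% or 5% against a true 15%, and a false gap between periods of about 3 points for shares of 50% and 30%. These figures assume that no survivors are excluded, and they would be smaller otherwise. They illustrate direction and order of magnitude; they are not estimates for this hospital. The air-leakage boundary is a minor clarification.

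**What to change.** 1. Remove discontinuation of treatment from the exclusion criteria. Keep these infants in the survival, mortality and BPD denominators, classified by vital status at 36 weeks where known, so that a death is shown as a death.
2. Limit exclusion for incomplete information to records that lack what is needed to establish eligibility or group assignment. Treat missing outcomes as missing data, with a best-case and worst-case bound.
3. Report by group the numbers who discontinued, whose record was unusable and whose outcome is unknown.
4. State one time boundary that separates air leakage as a birth complication from air leakage as a secondary outcome. It should be the same in all groups. It should not be tied to the surfactant dose, because dosing windows differ by group (within 12 h for intubation, within 2 h for MISA), so a dose-based boundary would itself treat the groups differently.

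The cost is an amendment to the criteria, a bounding analysis, and a search for vital status among infants in the retrospective cohorts who discontinued. Some of that status will stay unknown and must be reported as such. Survival figures will probably look less favourable. The change is best made before the prospective cohort is analysed.
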